**METHODS**

The following evaluation forms , questionnaires and instrumental evaluation will be administered at the beginning of treatment to all patients in all groups :

- Measurement of the angle of inclination of the trunk, using markers placed on specific points of reference on the basis of criteria established by analyzing posturographic

- Measurement of the position of the center of mass (COM) through data extracted from platform to baropodometry

- Stabilometry to evaluate the COP displacement in static and instrumental FRT

- Berg Balance Scale to assess balance

- Diary of falls and FES (Fall Efficacy Scale) to monitor falls rate and fear of falling

- PDQ -39 to assess the quality of life

- UPDRS (II -III section ) to assess motor disability

These instrumental tests , clinical evaluation will be administered again at the end of the eight weeks of treatment, rehabilitation and after another eight weeks of follow up.

Duration of the research

For each patient, an initial assessment will be performed T0, another evaluation after 8 weeks of treatment T1 and a final evaluation T2 after 8 weeks. The duration of the research study for each patient was then 16 weeks.

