
**OBJECTIVE**

The objective of this preliminary study is:

- to verify if the proposed device (Equistasi) as a proprioceptive postural stabilizer may represent an innovative and effective treatment in association with a physiotherapy program in improving balance and posture alterations and in maintenaning the outcome

-verify if the improvement obtained on postural perturbations have a positive effect on postural stability and falls in PD.

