**STATISTICAL ANALYSIS**

They will be subjected to statistical analysis of the data derived from the stabilometric , posturographic evluation , as well as those from clinical scales . This clinical trial will use a sample of convenience, with the assumption that 40 participants would be ample to explore safety and feasibility. Given the small sample and the lack of normal distribution of most of the variables on Shapiro-Wilk test, non-parametric statistics will use. Initially, The data will be subjected to statistical analysis ANOVA in order to produce an analysis of variance univariate and then to test the hypothesis of equality of more medium .
A comparison will be made for all variables (extrapolated data from rating scales , posturographic test , and baropodometry stabilometry ) and for dependent samples for independent samples to evaluate both the variation within the group than those between the two groups. This will be done through the use of a T- test .
The number of patients included in the study is the minimum number to conduct a pilot study to have a statistical significance level . Patients will undergo randomization criteria following the Conshort Procedures for radomization.

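### The second objective links posture gains to stability and falls, but only group and time comparisons are planned, and falls have neither a named analysis nor a defined baseline period

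*Protocol*

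**What the plan says.** The Objective section of the protocol has two aims. The second is to "verify if the improvement obtained on postural perturbations have a positive effect on postural stability and falls in PD".

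Methods lists the measurements, among them the "Diary of falls and FES (Fall Efficacy Scale) to monitor falls rate and fear of falling". It says that these instruments "will be administered at the beginning of treatment to all patients in all groups", and again at the end of treatment and after follow-up. The schedule is "an initial assessment will be performed T0, another evaluation after 8 weeks of treatment T1 and a final evaluation T2 after 8 weeks", and "The duration of the research study for each patient was then 16 weeks".

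Statistical Analysis opens with "statistical analysis of the data derived from the stabilometric , posturographic evluation , as well as those from clinical scales". It then states that non-parametric statistics will be used, names ANOVA, and says "A comparison will be made for all variables". A parenthesis follows that lists rating scales, posturography, baropodometry and stabilometry. The comparisons are for dependent and independent samples, by t-test.

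**The concern.** The second objective asks about a link between two outcomes: does a patient whose posture improves also become more stable and fall less? The planned tests take one variable at a time and compare groups or time points. If they were carried out exactly as written, one of the trial's two stated objectives would have no result that bears on its wording.

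Falls are part of that objective and are weakly specified at both ends. On the analysis side, the diary is not named among the data to be analysed. On the data side, a diary handed out when treatment starts has no observation time behind it at T0. A later analysis plan can repair the first gap. It cannot recover a falls history that nobody asked for at T0.

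**Working it through.** **1. Timeline.** Inputs from Methods: 8 weeks of treatment, 8 weeks of follow-up, 16 weeks in total. 8 + 8 = 16 reproduces the stated duration, and 16 − 16 = 0 weeks remain before T0. The diary therefore yields two periods, T0-T1 and T1-T2, both after randomised treatment begins. Available from it: a between-arm comparison in each period, and a within-patient comparison of the two periods. Not available: change from a pre-treatment rate.

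**2. Objective against planned tests.**

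| Question | Planned comparison that answers it |
|---|---|
| Does the device change posture? | Between-arm test on trunk angle and related measures |
| Does the device change stability? | Between-arm test on Berg and stabilometry |
| Does improvement in posture go with better stability? | None |
| Does improvement in posture go with fewer falls? | None |

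The last two rows cannot be filled from group means. Suppose the device arm gains on trunk angle and on Berg. The t-tests give the same results whether the patients who gained on one are those who gained on the other or entirely different patients.

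**3. Falls in the analysis section.** The opening sentence names stabilometric and posturographic data and clinical scales. The later parenthesis names rating scales, posturography, baropodometry and stabilometry. The Falls Efficacy Scale is a rating scale and is covered, but it measures fear of falling. The diary count is in neither list.

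**4. What a link analysis could detect.** The protocol gives no alpha, power or effect size, so assume two-sided alpha 0.05 and 80% power. By Fisher's z, the detectable correlation is r = tanh((1.960 + 0.842)/√(n − 3)).
- n = 36: tanh(2.802/√33) = 0.45
- n = 40 (the figure in Statistical Analysis): 0.43
- n = 18 (one arm): 0.62

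An exploratory association is feasible, but only a moderate to strong one would show.

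**5. What a between-arm falls comparison could detect.** Assume m falls per control patient and negative binomial dispersion k, with 18 per arm. The variance of the log rate ratio is (1/m + 1/(m·RR) + 2k)/18, and the detectable RR solves |log RR| = 2.802 × √variance. For m = 4, k = 1: (0.25 + 0.791 + 2)/18 = 0.169, square root 0.411, times 2.802 = 1.152, so RR = exp(−1.152) = 0.32. Over m = 2 to 8 and k = 0.5 to 2, the detectable RR runs from 0.46 down to 0.16. At m = 1 it is 0.12 with k = 0.5, and none is found with k = 1 or 2.

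**6. Count model with prior falls against a t-test.** This was a simulation with inputs that are not from the documents: 18 per arm, mean 4 falls per 8 weeks, gamma frailty of shape 0.7 with period-specific gamma noise of shape 2 or 4, and a rank correlation between prior and diary falls of about 0.5-0.65. The F-test of the adjusted quasi-Poisson model rejected about 10% of the time under the null, so both tests were calibrated to 5%:

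| True rate ratio | t-test | Count model adjusted for prior falls | Gain, smallest to largest |
|---|---|---|---|
| 0.5 | 21-23% | 24-35% | 24 − 23 = 1 to 35 − 21 = 14 points |
| 0.3 | 49-55% | 58-75% | 58 − 55 = 3 to 75 − 49 = 26 points |

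**The case against.** The strongest reply is that the study is a pilot on a convenience sample, that a separate analysis plan may exist, and that the method for one outcome can properly be left to it. That has force for the choice of falls model, and the particular count model proposed is partly a matter of preference. It does not cover the mismatch between an objective and an analysis that the same protocol states, or a baseline that must be collected at T0.

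Three stronger readings are tempting, and the protocol does not support them.
- **A reader might infer that falls are assigned a paired t-test.** The words "A comparison will be made for all variables" taken alone suggest it, but the parenthesis that follows omits the diary, and the same section says that non-parametric statistics will be used. What can be said is that falls have no named analysis. If the phrase is taken literally, they would get t-tests, which suit skewed counts poorly.
- **A reader might infer that nothing planned bears on the second objective.** The between-arm tests on Berg and stabilometry do address the device's effect on stability. Only the link from posture change to stability and falls is missing.
- **A reader might infer that the falls data are unusable without a baseline.** A randomised between-arm comparison needs none, and a look-back at T0 is unstated but not excluded. What is lost, as the diary is described, is change from before treatment.

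It is also fair to say that the power gain in the working is not purely a model effect, because the count model uses prior falls and the t-test does not.

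**Conclusion.** The concern holds in this form. The second objective asks for a relation that no planned analysis estimates. Falls, which that objective names, have no clearly assigned analysis and no defined pre-treatment period. The mismatch and the missing window follow from the protocol's own text and need no assumption beyond the natural reading that the diary begins when it is first administered.

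The size of the power loss does rest on assumptions, since the protocol gives no fall rate or dispersion. Under those assumed, the adjusted count model gains from almost nothing to a useful amount. Even then its power at a rate ratio of 0.5 is no more than about 35%, so falls should be reported as an estimate with its interval and not as a confirmatory test. The point deserves correction before enrolment but does not threaten the trial's main comparison.

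**What to change.** 1. Reword the second objective as the randomised effect of the device on postural stability and falls. Add one exploratory regression of T1 stability and falls on change in trunk angle, adjusted for arm and T0 values, and label it as association. Posture change is not randomised, so it cannot show that posture gains cause the rest.
2. At T0, record by recall the number of falls in the preceding 8 weeks, to match the length of each diary period.
3. Name the falls analysis: diary falls compared between arms over T0-T1 and over T1-T2, as a rate ratio with 95% confidence interval from a count model (negative binomial or quasi-Poisson), with log(diary days) as offset and prior falls as covariate, for example log(prior falls + 0.5). Take the p-value from a permutation test, because the model's own F-test rejects too often at this sample size. Use this instead of a t-test for falls.

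The cost is one question at T0 and a little more analysis. The drawback is recall error in the baseline count. Because recall is taken before treatment, that error mainly weakens the covariate and does not bias the comparison between arms.

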**Ethical considerations and evaluation of the benefit / risk ratio**

The benefit that patients will gain from participation in this study will be to receive a novel alternative and innovative treatment for postural alterations and balance problems , as it is proposed a typology of intervention based on the use of an innovative device Equistasi and furthermore a possible response to treatment of postural changes and balance problems , which currently represent a significant problem that can seriously affect the quality of life of patients with Parkinson's disease .
In addition, participating in the study, patients will make an important contribution to scientific research in the field of Parkinson's disease .
Patients included in the study will not change medications during the trial.
No risk has been described in the literature except for a skin allergy due to the patch which is used to apply the device.

**FUNDING**

Patients included in the study will not incur any costs as the device will be provided for free grant for scientific research by the Company Equistasi, also instrumental examinations and evaluations will be supported entirely by the Institute which will be held at the project research.
